#### Data storage and management

Data management will be conducted by the data management team of the clinical study center (CSC) of the Charité – Universitätsmedizin Berlin and the Center for Stroke Research Berlin (CSB). The clinical data of each patient will be pseudonymized using a unique identification number (pseudonym) created and assigned by the data trust center of the Charité (CHA-THS). Identifying data will be stored separately from the pseudonymized clinical data at the respective MSU platforms. Identifying data can only be accessed by the study teams of the respective MSUs according to a predefined concept of access rights and rules. Pseudonymized study-related data can be accessed by the study teams of the respective MSUs as well as the leading scientists and the biostatistician according to a predefined concept of access rights and rules. A statistical analysis will be conducted based on pseudonymized data.

ProGrEss-Bio uses an open-source electronic data entry and data management system (REDCap). Pseudonymized data will be collected using a web-based central eCRF on a tablet. Identifying data will be deleted after the completion of the study and will be stored for 10 years within the CHA-THS before being deleted, allowing no depseudonymization of the results.

#### Primary analysis

The prehospital distinction between patients with AIS and ICH without cerebral imaging and solely based on a single or a combination of blood biomarkers.

#### Secondary analysis

The prehospital distinction between patients with a stroke and SM without cerebral imaging and solely based on one or a combination of blood biomarkers.

#### Tertiary analysis

Determination of the kinetics of blood biomarkers within the acute phase of a stroke (≤4.5 h after symptom onset) by drawing blood directly after MSU arrival at the scene and 20–60 min later to detect and observe early changes in the concentrations of blood biomarkers.

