**Figure 2 F2:**
[figure not shown]
Conduction of the study. Procedure for including patients in the study is shown in chronological order from left to right. Boxes in red describe procedures during routine emergency treatment, and boxes in blue describe study-specific procedures. Blood samples will only be analyzed in cases where the patient or legal representative gives written informed consent. The blood sample is temporarily stored in the fire or rescue station and later in a biobank.

In contrast to many other studies, we plan to use a broad spectrum of potential biomarkers using a so-called “multi-omics” approach [proteins (proteomics), genes (genomics), ribonucleic acid (RNA [transcriptomics]), and metabolites (metabolomics)]. A second study-related blood sample will be collected from AIS and ICH patients 20 to 60 min after the collection of the first sample, usually done upon the patient's arrival at the hospital, the study allows for the examination of concentration changes and kinetics in the early phase. We plan to include 300 patients in this study. The study will be initially implemented at one MSU (STEMO 3600) and then rolled out to the other two MSUs. Universal trial number (UTN): U1111–1258-2477.

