### Study population

#### Inclusion criteria

Participants are eligible for the study if they meet the following inclusion criteria:

Age ≥ 18 years.Suspected or possible stroke or SM based on the initial assessment of the treating MSU neurologist.Symptom onset of ≤4.5 h before the collection of biomarkers.Written informed consent will be obtained from the participant or their legal representative. Informed consent can be given up to 12 weeks after the collection of the biomarkers, but before further analyses, either by the patient or their legal representative.

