#### Primary and secondary targets

As this is an explorative study (discovery phase), the primary target is to identify a single blood-based biomarker, or a panel of biomarkers, with strong differentiation between the AIS and the ICH groups, i.e., to identify candidates for a prediction model that will then be tested and refined in a subsequent study.

The same is true for the secondary target, namely, to identify a single blood-based biomarker or, again, a group of markers with great differences between stroke and SM patients.

To this end, the absolute values of blood biomarkers and their kinetics in AIS and ICH patients will be determined. We expect a change in the concentration of biomarkers over time in the acute phase after AIS and ICH patients due to vascular injury and subsequent neuronal cell injury, whereas we expect no such changes in SM patients.

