### Collection and processing of data and samples

#### Blood sampling and processing

The first study-related blood sample will be taken after all steps of the necessary emergency treatment are completed. A second study-related blood sample in AIS or ICH will be drawn between 20 and 60 min subsequently, if possible, i.e., the patient will not be transported by regular ambulance alone or for other reasons, e.g., life-saving therapies are required, making the collection of a second blood sample impossible.

All tubes for each study participant will be individually pre-labeled, pre-coded, and packed with a unique identifier (ID). Identification of the study participants will only be possible with this unique ID. The following steps are shown in detail in Figure 3. Two ethylenediaminetetraacetic acid (EDTA) tubes (6 and 3 ml), one heparin tube (5 ml), one serum tube (5 ml) (VACUETTE^®^, blood drawing tubes, from Greiner Bio-One, Austria, Kremsmünster), a Tempus™-tube (3 ml) [TEMPUS™, blood ribonucleic acid (RNA) tube, Applied Biosystems™ by Thermo Fisher Inc., United States, Waltham, MA], and a small amount of blood in a full blood tube for international normalized ratio measurement and dry blood cards will be used for blood sampling in study participants. The serum tube will be collected first, and the Tempus™-tube will be the last.

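### The kinetic analysis claims a ≤4.5 h window that second samples can exceed by up to an hour, and separately it takes no account of treatment tied to the AIS diagnosis

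*Protocol article*

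**What the plan says.** **Window.** The Tertiary analysis section places the kinetics "within the acute phase of a stroke (≤4.5 h after symptom onset". The Inclusion criteria set one time limit: "Symptom onset of ≤4.5 h before the collection of biomarkers". The Study design section (text after the Figure 2 caption) adds: "A second study-related blood sample will be collected from AIS and ICH patients 20 to 60 min after the collection of the first sample", usually on arrival at hospital. Blood sampling and processing repeats the 20 to 60 min interval. None of these sections gives the second sample its own limit relative to onset.

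**Timing of the first sample.** The Tertiary analysis has it as "drawing blood directly after MSU arrival at the scene and 20–60 min later to detect and observe early changes in the concentrations". Blood sampling and processing has it differently: "The first study-related blood sample will be taken after all steps of the necessary emergency treatment are completed".

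**Expected cause of the change.** Primary and secondary targets states: "We expect a change in the concentration of biomarkers over time in the acute phase after AIS and ICH patients due to vascular injury" and the neuronal cell injury that follows it. It expects no such change in stroke mimics (SM). Treatment is not mentioned as a possible cause.

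**Who has a pair.** Second samples are planned for AIS and ICH only, and only where feasible: "the patient will not be transported by regular ambulance alone or for other reasons, e.g., life-saving therapies are required".

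**Use of the kinetics.** The Secondary hypothesis says kinetics may improve discrimination, and the Conclusions say that their discriminatory value will be investigated. The Biomarkers section lists plasminogen and D-Dimer among the markers to be measured.

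**The concern.** The stated window and the sampling rules cannot both hold for every pair. A report of kinetics within 4.5 h of onset would include samples taken after it.

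The treatment point is different in kind. The Abstract and Introduction say that the mobile stroke unit (MSU) brings imaging and intravenous thrombolysis to the patient, and that hemorrhage must be excluded before thrombolysis. Thrombolysis therefore goes with the AIS side of the AIS-versus-ICH contrast. If concentrations move because of a drug, the movement appears only after imaging has settled the diagnosis. The Introduction and Outcomes sections aim at diagnosis without imaging in regular ambulances. A change that exists only after imaging and treatment cannot serve that aim, yet it could go forward to the next phase as a kinetic candidate. Plasminogen and D-Dimer belong to the fibrinolytic system, so a thrombolytic effect on them is easy to foresee.

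Nothing in the design would show up a change unrelated to injury. Without a second sample in SM patients, the expectation of no change there cannot be tested.

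**Working it through.** **1. Window**

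Inputs: latest first sample 4.5 h after onset (Inclusion criteria); interval 20 to 60 min (Study design; Blood sampling and processing); claimed window ≤4.5 h (Tertiary analysis).

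Time of second sample = time of first sample + 20 to 60 min.

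- First sample at 4.5 h: second at 4 h 50 min to 5 h 30 min. The latest permitted second sample is 4.5 h + 60 min = 5.5 h.
- Second sample certain to be inside: first + 60 min ≤ 4 h 30 min, so first ≤ 3 h 30 min.
- Second sample certain to be outside: first + 20 min > 4 h 30 min, so first > 4 h 10 min.
- In between (after 3 h 30 min, up to 4 h 10 min), it depends on the actual interval.

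The ≤4.5 h figure does not follow from the article's own timing rules. The share of pairs affected depends on the distribution of onset-to-sample times, which the article does not give.

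**2. Treatment under each stated timing of the first sample**

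| First sample | Where thrombolysis can fall | What the change in treated AIS can contain |
|---|---|---|
| Directly after MSU arrival (Tertiary analysis) | Between the samples | Injury plus onset of drug effect |
| After emergency treatment is completed (Blood sampling and processing) | Before both samples | Injury plus continuing drug effect; the baseline may be affected too |

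The article does not say whether an infusion may still be running between the samples. Neither row isolates injury, so the comparison needs treatment status under both.

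**3. Illustration of size (assumed inputs)**

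Assume no true difference in kinetics, a fraction f of AIS pairs treated between samples, a shift of s standard deviations in those patients, and no treatment effect in ICH. The mean difference is f·s. The AIS variance is 1 + s²f(1−f) and the ICH variance is 1, so

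d = f·s / √(1 + s²f(1−f)/2).

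- f = 0.5, s = 0.5: d = 0.25/√1.03125 = 0.25.
- f = 0.5, s = 1: d = 0.50/√1.125 = 0.47.

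With a two-sided normal test at alpha 0.20, a difference is declared in 44% to 80% of studies with 40 pairs per group and in 61% to 96% with 80 per group, against 20% by chance. With f from 0.3 to 0.7 and 40 per group, the range is 29% to 96%.

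The treated share, the shift and the number of pairs are not in the article. The group sizes 40 and 80 come from the Power analysis section, where 40 per group refers to AIS versus SM and 80 to AIS versus ICH; neither is a number of pairs. Alpha 0.20 is stated there for the primary and secondary targets, not for kinetics. These rates show what an assumed bias would do, not that one is present.

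**The case against.** The strongest reply starts with the sampling procedure. It puts emergency treatment before the first sample, so a before-and-after-treatment change need not arise. The statement about injury is an expectation in a discovery study, and the tertiary analysis is worded as observation; no test of AIS against ICH change scores is specified. A rule for treated and untreated patients is something an article may leave to the full protocol or analysis plan. Treatment times may already be recorded, since the Abstract says that medical information goes into the eCRF. Candidates will in any case be tested in a new sample.

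Much of this stands. It rules out the stronger inference that AIS-versus-ICH kinetics in this study would be treatment effects. Treatment between the samples is only one of two readings, and the article does not formally attribute the change to injury. But the reply leaves the contradiction over the first sample unresolved, and under the procedure's own timing a continuing drug effect remains possible. The Secondary hypothesis and Conclusions do want kinetics for discrimination, so treatment status matters.

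Two further inferences are not supported:

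- **Window overrun as evidence of treatment effect.** It is a separate inconsistency and says nothing about what causes the change.
- **Paired AIS patients being mainly treated ones.** Losing pairs to regular ambulance transport might favor treated patients, but losing pairs when life-saving therapies are required might do the opposite. Selection is possible; its direction is unknown.

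On the window, a reader might take the 4.5 h entry limit to cover both samples. The article does not say so, and the point would then need stating.

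**Conclusion.** The window statement is wrong as written: second samples can lie up to 1 h beyond it. This rests only on the article's own limits and is a matter of arithmetic.

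The treatment point is a well-founded, inexpensive improvement rather than a demonstrated bias. It rests on thrombolysis being tied to the AIS diagnosis, injury being the only cause named for the expected change, kinetics being wanted for discrimination, and the absence of a planned second sample in SM. It holds under either stated timing of the first sample, and the two statements must be reconciled. Its size cannot be derived from the document; the rates shown above are illustrative only. A fuller protocol or analysis plan may already separate treated from untreated patients.

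**What to change.** 1. **Window.** Either limit the ≤4.5 h kinetic claim to pairs whose second sample is within 4.5 h of onset, or restate the window as up to 5.5 h for the second sample.
2. **First-sample timing.** Reconcile the Tertiary analysis with Blood sampling and processing, so that the position of the first sample relative to treatment is stated once.
3. **Treatment status.** Use the clock times of both samples and of each acute treatment. Present AIS and ICH kinetics by treatment status. Base any claim of diagnostic kinetics on patients not yet treated by the second sample, and show treated AIS separately as a description.
4. **Elapsed time.** Analyze the change by the actual time between samples, since the interval varies threefold (20 to 60 min).
5. **Reporting.** State that pairs are selected by feasibility, in an unknown direction, and that the expectation of no change in SM is not tested.

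The cost is wording, plus a few time fields if the eCRF does not already hold them. The real downside is fewer pairs in the untreated comparison, and in the ≤4.5 h set if the claim is restricted. No change to care or to its timing is needed.

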### Definitions

The main diagnosis of the hospital discharge letter will be used to decide whether the patient suffered from an AIS, an ICH, or an SM. In cases of more than one diagnosis, the most likely differential diagnosis was used. In cases where no clear distinction between AIS, ICH, and SM was possible, patients were excluded from the analysis. TIA patients will be considered to be part of the AIS group, but how many patients suffered from a TIA and AIS will be reported.

Stroke entities or SMs in the literature are usually defined by the following definitions:

Stroke:

Ischemic stroke: An episode of neurological dysfunction caused by focal cerebral, spinal, or retinal infarction but infarction caused by the brain, spinal cord, or retinal cell death is attributable to ischemia, based on pathological imaging or clinical evidence of cerebral, spinal cord, or retinal focal ischemic injury based on symptoms persisting ≥24 h or until death and other excluded etiologies (36).Intracerebral hemorrhage: Rapidly developing clinical signs of neurological dysfunction attributable to a focal collection of blood within the brain parenchyma or the ventricular system that is not caused by trauma (36).

Further details on the diagnosis of stroke can be found elsewhere (36, 37).

Stroke mimics:

Certain diseases such as syncope, epileptic seizures, hypoglycemia, hyperglycemia, migraine aura, dissociative disorder, and so on. A stroke is initially clinically suspected, but the diagnostic criteria for stroke are not fulfilled (36).

#### Sample size

In this explorative study (“discovery phase”), no decisive sample size calculation can be performed, as the effect size of the parameters with respect to predicting to which group the patients belong will become clear only through and at the end of this study. Thus, the envisaged sample sizes will be used to determine the effects that can be detected with them (see next section).

Since, for all patients, the ultimate diagnosis (AIS, ICH, or SM) is known only in retrospect, patients will be included until the targeted sample sizes of all groups are completed or the anticipated study end is reached.

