**Methods and analysis:**

We plan a prospective, observational study involving 300 patients with suspected stroke and symptom onset of ≤4.5 h before the collection of biomarkers. Study participants will be recruited from three sites in Berlin, Germany during MSU deployments. The focus of the study is the collection of blood samples from participants at the prehospital scene and from participants with AIS or ICH at a second-time point. All samples will be analyzed using targeted and untargeted analytical approaches. Study-related information about participants, including medical information and discharge diagnoses from the subsequent treating hospital, will be collected and documented in an electronic case report form (eCRF).

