### Power analysis

For the primary target, the data from 80 AIS and 80 ICH patients will be used. Given the elevated alpha = 0.20 used here, the standard value of beta = 20% (corresponding to a power of 80%), and the use of the Chi-squared test, the sample will be sufficient to detect all large, medium, and small effects of w ≥ 0.17 (Cohen's d ≥ 0.30). For the secondary target, for which data from 40 AIS (taken as a random sample out of the pool of 80 patients) and 40 SM patients will be used, the numbers will suffice to detect large, medium, and some smaller effects with w ≥ 0.24 (Cohen's d ≥ 0.40) and thus all effects with a minimally clinically important difference (MID).

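### The Power analysis section limits the two main comparisons to 80 AIS, 80 ICH and 40 SM although 300 patients are planned, and its detectable effect holds only if 80 ICH are reached

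*Protocol article*

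**What the plan says.** All references are to the protocol article.

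- **Enrolment.** Study design states: "We plan to include 300 patients in this study". The abstract gives the same number and adds: "All samples will be analyzed using targeted and untargeted analytical approaches".
- **Primary target.** Power analysis: "For the primary target, the data from 80 AIS and 80 ICH patients will be used".
- **Secondary target.** Power analysis: "40 AIS (taken as a random sample out of the pool of 80 patients) and 40 SM patients will be used".
- **Stopping.** Sample size notes that the diagnosis is known only in retrospect, then: "patients will be included until the targeted sample sizes of all groups are completed or the anticipated study end is reached".
- **Detectable effects.** With alpha 0.20 and 80% power, Power analysis gives w of at least 0.17 for the primary target and w of at least 0.24 for the secondary. Both are stated for full groups only.
- **Candidate selection.** Statistical analysis draws the primary predictors from all the proteomics and metabolomics data that are available. For the secondary target it puts AIS, with ICH in brackets, on the stroke side against SM.
- **Other uses and losses.** Definitions excludes patients who cannot be clearly classified. Tertiary analysis (kinetics) names no cap.

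**The concern.** Three statements are not tied together: 300 planned patients, analysis sets of 80, 80 and 40, and a stopping rule that can end recruitment before the groups are full.

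First, group membership cannot be controlled at enrolment. While the ICH group fills, further AIS and SM patients will accrue. Their samples are collected and assayed, but the Power analysis section gives them no place in either comparison. The secondary target goes further: it sets aside half of the 80 AIS at random and leaves out ICH, although Statistical analysis puts ICH on the stroke side.

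Second, the sample is said to be sufficient for w of 0.17 without a condition. That depends on the ICH group, the one whose size the plan does not secure.

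The study screens candidates at p < 0.20 and carries them into a later sample. Lost power here means a useful marker is not carried forward, and the later phase has no stated route to recover it.

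**Working it through.** **1. Inputs.** 300 patients (abstract, Study design); 80 AIS, 80 ICH, 40 AIS within the 80, 40 SM, alpha 0.20, power 80% (Power analysis). The documents give no ICH or SM share, so those are assumed over a range.

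**2. The plan's own figures.** Chi-squared test, 1 df, noncentrality N·w².
- Primary: 160 × 0.17² = 4.62, power 80.8%.
- Secondary: 80 × 0.24² = 4.61, power 80.7%.

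Both w values reproduce. For two equal groups d = 2w/√(1 − w²), so w = 0.17 is d = 0.345 and w = 0.24 is d = 0.494. The article prints 0.30 and 0.40 in brackets. That mismatch is a separate matter. To keep it out of this point, the primary calculations use d = 0.345.

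**3. Head count.** 80 + 80 + 40 = 200, because the 40 AIS of the secondary target lie within the 80. 300 − 200 = 100.

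**4. ICH share.** If 300 is the ceiling, 80 ICH means 80/300 = 26.7%. Even at a true share of exactly 26.7%, the binomial chance of at least 80 ICH among 300 is about 52%; at an assumed 20% it is 0.3%.

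**5. Primary target by ICH yield.** SE = √(1/n_ICH + 1/n_AIS); power from the two-sample t test, two-sided alpha 0.20, noncentrality 0.345/SE. Detectable d at 80% power ≈ (1.282 + 0.842) × SE. In the uncapped columns n_AIS = 300 − 40 − n_ICH.

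| ICH (assumed) | Power, 80 AIS | Detectable d | All AIS (SM = 40) | Power | Detectable d |
|---|---|---|---|---|---|
| 30 | 62.9% | 0.45 | 230 | 69.0% | 0.41 |
| 45 | 71.4% | 0.40 | 215 | 79.4% | 0.35 |
| 60 | 76.9% | 0.36 | 200 | 85.5% | 0.31 |
| 80 | 81.5% | 0.34 | 180 | 90.0% | 0.29 |

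Hand check, 30 ICH and 80 AIS: SE = √(1/30 + 1/80) = 0.214; 0.345/0.214 = 1.61; Φ(1.61 − 1.28) ≈ 63%.

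**6. Dependence on the SM share.** With 300 enrolled and 60 ICH, n_AIS = 240 − n_SM.

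| SM (assumed) | AIS | Power at d = 0.345 |
|---|---|---|
| 40 | 200 | 85.5% |
| 100 | 140 | 82.9% |
| 160 | 80 | 76.9% (no gain) |

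**7. Secondary target.**
- 40 AIS and 40 SM: SE = √(1/40 + 1/40) = 0.224. Power at d = 0.40 is 69%.
- 80 AIS and 40 SM: SE = √(1/80 + 1/40) = 0.194. Power is 78%.
- At d = 0.494, the equivalent of w = 0.24, the same change takes power from 82% to 90%.

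This gain needs no assumption about the case mix beyond the article's own 80 AIS and 40 SM.

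**The case against.** Several objections have weight.

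- **300 is a plan, not a ceiling.** The stopping rule does not mention it. So the 26.7% is conditional, and a reader who infers that the study requires 27% ICH goes beyond the text.
- **The sizes are already described as targets.** Sample size also says that no decisive calculation is possible and openly allows an end at the study's planned close. Stopping on a calendar date is ordinary. This stands. What remains is that the detectable effect is stated only for full groups.
- **Surplus patients may be used after all.** Statistical analysis refers to all available data, and the kinetics analysis has no cap. One might infer that a third of the patients will be thrown away, but the article does not establish that. The phrase about available data describes omics data, however, while Power analysis names the patients, so the two sections need aligning.
- **Some of the 100 may be a buffer.** Unclear diagnoses are excluded, and samples without consent within 12 weeks are destroyed. The article does not say whether 300 is counted before or after these losses, so 100 is an upper bound.
- **The gain from using all AIS is a best case.** It assumes SM stays at 40; step 6 shows it can vanish.
- **This is an exploratory screen with balanced groups by choice.** Balance is efficient when the total is fixed. It is no reason to leave out patients already sampled and assayed, and logistic regression does not need equal groups.

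**Conclusion.** The point holds in a limited form. As written, the Power analysis section restricts the two main comparisons to 200 different patients when 300 are planned. Up to 100 have no stated role in those comparisons, fewer after exclusions.

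The w of 0.17 is correctly computed, but it depends on 80 ICH, which the stopping rule does not guarantee. With AIS held at 80, power at that effect falls from about 81% to 77%, 71% and 63% if 60, 45 or 30 ICH are obtained. Using all AIS recovers up to 6 to 9 percentage points, depending on the SM share. The firmest gain is in the secondary target: about 9 points at d = 0.40 from not discarding 40 AIS at random.

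A reader might infer that an ICH shortfall is likely. The documents show that one is permitted; they give no ICH share from which to judge its probability. The yields above are assumptions. The issue affects efficiency and clarity and does not invalidate the study.

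**What to change.** 1. In Power analysis, define the set for both targets as all eligible, consented patients with a classified discharge diagnosis. Drop the random subsample of 40 AIS.
2. Align Statistical analysis and Power analysis: say which patients enter each comparison, and whether ICH belongs to the stroke side of the secondary target.
3. In Sample size, say whether 300 or the group targets govern recruitment, and whether 300 is counted before or after exclusions.
4. State the detectable effect as conditional on the achieved ICH number, in a short table (for example 30, 45, 60 and 80 ICH), with the assumed SM number shown.

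This takes a few sentences and one small table, with no extra patients and no assays beyond those already planned. The cost is unequal groups and a less favourable stated figure if few ICH patients are recruited.
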